### Host genetic testing

Investigators will perform targeted analyses of genetic polymorphisms within host genes reported to influence the rates of pathogen acquisition and/or disease severity. These genes may function pathogen host restriction, and innate and adaptive immune system responses. Host restriction genes of interest include but are not limited to entry receptors and post-entry factors. Targeted genes of the innate immune system will include, but not limited to, killer immunoglobulin receptors (KIR) and cognate Class 1 ligands; dendritic cell-specific intercellular adhesion molecule-3-grabbing non-integrin (DC-SIGN); and toll-like receptors (TLR). Those involved in humoral and cell-mediated immune responses will include Fcγ receptors, capable of binding diverse immunoglobulin isotypes; and the alleles comprising Class I HLA-A, -B, and -C loci, respectively. HLA typing procedures that will be used in this study have yet to be validated for clinical use, but represent essential research tools for the analyses of adaptive immune responses across multiple types of infections. HLA typing and other genetic testing data will be only collected from those who have provided specific consent in a separate genetic testing consent form. Data will be unlinked from personal identifiers, and reported in aggregate for the populations studied.

### Transcriptomics

Isolated cross sectional identification of genomic expression is fraught with a lack of reproducibility due to patient heterogeneity, latent confounding and non-biological variation. Importantly, the quantitative approach developed for analyzing associations between within-patient gene changes and clinical outcomes conducted longitudinally should provide more robust predictions of outcomes than single measurements of gene expression controlling for a bulk of the intra-patient confounding and heterogeneity. The challenge is how to accurately interrogate and associate early longitudinal gene expression measured at multiple time points with long term clinical trajectories captured by a constellation of clinical variables. We seek to capitalize on the longitudinal structure within an individual, combining bioinformatics and statistical tools to elucidate pathway dynamics from the gene expression data. For host transcriptomics, approximately a small amount of blood will be collected into commercial blood RNA tubes, processed at the hospital, and then frozen for transport to the laboratory. Total RNA will be extracted with commercial kits and subjected to quality control. Specimens meeting quality control criteria will be further processed for use on a human gene expression microarray. Extracted RNA will be reverse transcribed and amplified using kits. Arrays will be scanned raw images will be processed using proprietary software. The gene lists generated will be formatted and subjected to network or biological pathway analysis. Networks will be further analyzed for relevance to the particular biological system and clinical setting.

### Study instruments

The following instruments have been produced to provide measure of the variables of interest:

### Questionnaires

Some of the key variables will be measured through questionnaires administered by the study nurse. Three types of questionnaires will be used to collect information: Screening questionnaire (to be completed during the screening visit – see Additional file 1); Enrolment questionnaire (to be completed after RT-PCR for ZIKV positive results are delivered – see Additional files 2 and 3); and Follow up questionnaires (see Additional files 4 and 5).

**Screening questionnaire**: completion will be performed at the first visit by the study nurse. The same questionnaire will be applied to males and females and includes questions on social demographic data.**Enrolment questionnaire**: this is a gender specific questionnaire divided by sections as follows:
Socio demographics data (more detailed in comparison to the screening questionnaire)Sexual and Reproductive health historyEpidemiological dataComorbiditiesVaccinesHealth assistanceSexual activity
c)**Follow up questionnaire**: this is also a gender specific questionnaire which will be applied at the follow up visits by the study nurses. The questionnaire will collect information on the convalescent phase of the ZIKV infection and will comprise questions on health and wellbeing and sexual activity.

**Consultation forms** (see Additional files 6 and 7).

These are medical forms to be completed by the study consultant in infectious disease during medical consultations. Information collected will include:Signs and symptoms: onset and end of each symptom in both phases, acute and convalescent.Physical examination: general, circulatory, respiratory, neurological and rheumatological.

### Data quality assurance

Quality checks will be built into the data management system used by the study team and quality control checks of critical data points will be employed to ensure standardization and validity of the data collected. In case of invalid answer an alert will be issued providing the possible answers for that specific question. A manual as well as training of persons who will be involved in the completion of the questionnaire will be provided.

Data queries will be generated and conveyed to each participating site. Ownership of the data entered into the central database will remain with the site that contributed it.

The database will be installed in a dedicated server for the management of the data in Java©. The server will allow authorised members of the study team to enter online data which will provide great flexibility as data entry will be possible at the point where the data is being collected. At the same time, consistency of answers will be verified during the process of questionnaire completion. This will be possible through any internet navigator. In addition to the security measures for accessing the system there will be automatic backups.

Nurses will use ultrabook (tablets) for entering the questionnaire responses collected during the visits to the index case household or at the collaborating clinics. Access to the database will be given to those individuals who will be entering and analyzing the data.

Members of the team with access to the database will be trained before receiving access to the productive server. Likewise only trained interviewers will be used for the interviews and specimen collection. The topics included in the questionnaires include asking for information that may be perceived as sensitive and efforts will be made to ensure a private setting and calm environment to assure internal validity of the data collected.

Handling and treatment of biological sampling and specimen will follow standard operating procedures. Specimens will be handled at appropriate laboratories following relevant protocols.

Study staff will review data collected and entered for quality and consistency. Data quality reports will be developed and generated weekly with feedback to study staff.

### Data management

WHO in collaboration with the Ministry of Health data management team will design an electronic web based database, compliant with good clinical practice. Information collected from the questionnaires and clinical forms will be entered from each site and monitored by a member of WHO team. For data capture the platform to be used will be OpenClinica and analyses will be performed with SAS. All people who collect and analyse the data will be given access to the database. Laboratory results will be imported from an electronic management system utilized by Public Laboratories in Brazil.Data entry, validation, and query resolution will run in parallel with recruitment.No patient-identifying information will leave the country and will be managed by the collaborating clinics. Each clinic will capture their own data and export to a central unit for analysis which will be performed by a statistician contracted by the study. Individual records and the key linking the participant code number will be kept secure, accessible only to the local study team under the supervision of the study PI.Interview data will be organized in databases stored on secure local servers within each study site and it will be backed-up regularly. Collected data will be directly recorded on computers or tablets to minimize data recording and entry errors and minimize delays in data availability. If paper forms must be used, interview responses will be entered into the database either daily or as a group at the close of data collection; and 5% of entered forms will be re-checked to identify any problems with data entry accuracy that must be addressed.Electronic equipment and files will be kept password-protected.Paper forms and electronic devices will be kept locked when not in use.All patient identifiers will be removed from the dataset before analysis and replaced with a unique participant code that can be linked back to individuals via a master key at a centralized secure server and database.Paper interview forms, if used, will be destroyed within five years, according to the Brazilian National Regulations (Resolution 466/2012), after all data are entered and verified. However, questionnaires administered by the study nurses are meant to be completed electronically.Laboratory staff will identify specimens only by the labelled study ID, and will not have access to any personally identifying information.Study nurses will provide laboratory results only in person and only to participants who (1) return for a follow-up study visit; (2) present their study ID card or confirm their identity and study ID number; and (3) agree to receive their own results. Individual results will not be shared with anyone other than the study participant. Results will be presented according to a script.

### Data analysis plan

Descriptive analysis of the study participants will be performed by a statistician located at the country where the study is undertaken.WHO technical assistance may be provided as needed for these and any additional analyses of the study data. Any further statistical analysis will be conducted using adequate statistical program packages.Viral persistence time will be measured in days from time after symptom onset or identification of the infection in asymptomatic participants.Measures of interest are:○ Maximum duration of tissue culture-positive results for ZIKV for each of the body fluids specimen types;○ Maximum duration of other markers of ZIKV infection tested for each of the body fluids specimen types tested for these markers;○ Viral load as determined by cycle threshold (CT) value and/or international units per mL (IU/mL) for each specimen with positive RT-PCR result;○ Comparison of ZIKV genetic sequences between participants and from specimens collected over time from the same participant;○ Rate of co-morbidity with HIV, syphilis, dengue and chikungunya viruses;○ Correlation between positive RT-PCR and culture tests for each body fluid type.Viral persistence in a body fluid at a certain period in time, will be analyzed in relation to host factors such as age, sex, co-morbidity including HIV, syphilis, dengue virus and chikungunya virus and its clinical characteristics, severity of the symptoms, as well as presence of IgM and IgG antibodies in serum, and environmental factors.Participant information on sexual history will be analyzed for frequency and type of sex (protected/unprotected).Statistical methods:○ The baseline characteristics for the entire sample of recruited participants will be described;○ Frequencies and percentages will be reported for categorical variables. For quantitative normally distributed variables, the number of subjects, means and standard errors will be provided, while medians, interquartile range, minima and maxima will be reported for skewed non-normal quantitative variables;○ The analysis for the study outcomes will primarily be based on the eligible participants who tested positive for ZIKV in blood or urine at baseline;○ The Kaplan-Meier (K-M) survival analysis (non-parametric methods), will be used to analyze time to event outcomes (utilizing both right-censored and interval-censored techniques), K-M survival curves will be plotted and the Cox Proportional Hazards semi-parametric model to adjust for potential confounders/independent variables. Parametric survival models would also be explored;○ For the categorical (binary) repeated outcomes models that take into account correlation between outcomes collected over time will be considered. This would include GEE models, where relevant;○ Two-sided tests and 5% significance levels will be used and 95% confidence intervals for all relevant parameters. SAS statistical packages will be used for the statistical analyses;○ Open-ended questions will be listed and coded for meaningful comparisons of their distribution.

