### Sampling and sample size calculation

ZIKV is an emerging pathogen about which little information is known. This is a prospective observational cohort study, whose prediction of the exact sample size required cannot be prospectively determined. However, considering the scarcity of existing information on viral shedding, even a few participants would contribute to the body of evidence on the topic and lead to improved public health recommendations.

A multistage cluster sampling will be used to identify potential participants for inclusion and follow-up in the persistence cohort. All consecutive individuals RT-PCR positive for ZIKV in urine and/or blood identified during the screening process will be included in the cohort. In addition, all adult household/sexual contacts (symptomatic or asymptomatic) of these clinical cases, will be offered participation, and to be tested and included in the cohort if found RT-PCR positive for ZIKV in blood and/or urine.

The following is the rationale for estimating the sample size needed for body fluids other than blood, when we hypothetically estimate the prevalence of persistence will be 50% after 12 months. The below sample size calculations refer to estimating a population proportion at a certain point (or period) in time.

Using a population size (N) of 1,000,000 for finite population correction factor, and hypothesized rate of ZIKV persistence in at least one body fluid that is near 50% by the end of 12 months post-ZIKV infection, with a two-sided 95% confidence interval width of 10% (or margin of error (ME) of ±5%), a sample size of 385 males and 385 females who are either positive for ZIKV in urine or in blood at baseline will be needed.

The potential introduced design effect of the different clinic facilities used in the consecutive recruitment of study participants, will be explored both in stratified analyses by clinic, and in addition clinic will also be run as an independent variable in multivariate models.

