To account for the design/clustering effect at household level, we applied design effect DE of 1.5 assuming a cluster (family) size of 3 ZIKV-infected participants and an assumed an intra-cluster correlation (ICC) of 0.25, resulting into a sample size of 576 males and 576 females. We further assume that 10% of participants, index cases and household/sexual contacts, will be lost to follow up, by the end of the first year and hence the final sample size will be 634 males and 634 females. We rounded this number up to 650 males and 650 females. The sample size is tentatively estimated, given that there is little information on ZIKV persistence rates in bodily fluids, available in literature. The final sample size of 650 males and females is estimated for evaluation of the primary outcome which is the overall ZIKV persistence rate by 12 months (taking into consideration a design / clustering effect and loss to follow up). Since the role of different risk factors is not yet well known, the subgroup analyses will be done in an exploratory way and the effect of different factors on the primary outcome will be further explored in multivariable analysis models.

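### The sample size allows for household clustering (design effect 1.5), but no stated analysis method carries it into the standard errors

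*Protocol article*

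**What the plan says.** The section Sampling and sample size calculation describes multistage cluster sampling and offers enrolment to all adult household or sexual contacts who test positive. The target rests on a "hypothesized rate of ZIKV persistence in at least one body fluid that is near 50% by the end of 12 months", estimated to within ±5 points, which gives "a sample size of 385 males and 385 females". The text then says: "To account for the design/clustering effect at household level, we applied design effect DE of 1.5". The assumptions behind that figure are three infected participants per family and an ICC of 0.25. The target becomes 576 per sex, then 634 after a 10% allowance for loss, rounded to 650. The same section says that this size serves the primary outcome, the overall persistence rate by 12 months, with clustering taken into account.

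For the analysis, the article names two ways of handling dependence:

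- **Clinic.** Analyses will be stratified by clinic, and "clinic will also be run as an independent variable in multivariate models" (Sampling and sample size calculation).
- **Repeated measures in one person.** "For the categorical (binary) repeated outcomes models that take into account correlation between outcomes collected over time will be considered", with GEE as the example (Data analysis plan).

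Time-to-event outcomes will be analysed by Kaplan-Meier and by "the Cox Proportional Hazards semi-parametric model to adjust for potential confounders/independent variables", with parametric survival models to be explored. Tests are two-sided at 5%, with 95% intervals. Household does not appear as a cluster, stratum, frailty or variance unit in any of these methods.

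**The concern.** The article does say how it will treat correlated data, so this is more than an omitted detail. It names two sources and leaves out the only one to which it gave a number. A clinic covariate does not absorb correlation between people in one home, and a GEE for outcomes over time, as worded, groups visits within a person.

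If the household is left out, standard errors are too small wherever household members contribute similar information. That applies to the primary 12-month proportion, to Kaplan-Meier estimates, and to factors shared by a household. The last group matters because the primary objectives relate persistence to environmental factors, many of which are plausibly common to one home. The design would pay for clustering in recruitment and then report precision as though there were none.

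**Working it through.** **Inputs from Sampling and sample size calculation:** p = 0.50; margin ±0.05; two-sided 95%; population 1,000,000; cluster size m = 3; ICC = 0.25; loss 10%; final size 650 per sex.

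**1. The plan's own figures.**
- n = 1.96² × 0.25 / 0.05² = 384.15, or 384.00 with the finite population correction. The plan states 385.
- Design effect DE = 1 + (m − 1) × ICC = 1 + 2 × 0.25 = 1.5.
- 384.00 × 1.5 = 576, as stated.
- 576 × 1.10 = 633.6, so 634, as stated. Dividing by 0.90 would give 640; the rounded 650 covers both.

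The chain reproduces, and the design effect follows from the stated cluster size and ICC.

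**2. Interval for the primary proportion.** Evaluable per sex: 650 × 0.90 = 585.
- Households ignored: 1.96 × √(0.25/585) = 0.0405, or ±4.05 points.
- Households counted: 0.0405 × √1.5 = 0.0496, or ±4.96 points.
- Ratio 1/√1.5 = 0.816, so the unadjusted interval is 18% too narrow.

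Pooled over both sexes (1,170 evaluable), the same formulas give ±2.87 against ±3.51 points.

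**3. Coverage and type I error if households are ignored.** Coverage = 2Φ(1.96/√DE) − 1; type I error is its complement.

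| Design effect | Coverage of nominal 95% | Type I error of nominal 5% |
|---|---|---|
| 1.5 (m = 3, ICC 0.25) | 89.0% | 11.0% |
| 1.25 (m = 2, ICC 0.25) | 92.0% | 8.0% |

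A beta-binomial simulation of 195 households of three (585 people, p = 0.5, ICC 0.25, 20,000 runs) agrees: 89.4% coverage when households are ignored, 94.9% with a household-robust variance.

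**4. Sensitivity.** The article does not give the number of infected household members of the same sex. Assuming 1.5 to 3 of them and an ICC from 0.10 to 0.40, DE runs from 1.05 to 1.80 and coverage from 94.4% down to 85.6%.

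**5. Which tests are affected.** Simulation of 390 households of three (p = 0.5, ICC 0.25, 4,000 runs), with a two-proportion test that ignores households at nominal 5%:

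| Covariate | Type I error |
|---|---|
| Shared by the whole household | 11.3% |
| Independent of household | 5.0% |
| Index case versus contacts, within household | 2.5% |

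The direction of the error therefore depends on how the covariate is distributed within households.

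**The case against.** The strongest reply is that this reads intent from silence. The article is a condensed account with open wording: models will be considered, GEE is used where relevant. GEE and Cox can both take a household cluster or a robust variance, and an analysis plan that is not shown may say so. A reader might infer that every analysis will treat household members as independent. The article does not say that. What stands is the mismatch inside the article: it specifies how dependence is handled, and household is not on the list.

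Three further limits are fair:

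- **Not every test is too liberal.** Age, sex, co-morbidity, symptom severity and antibody status can all differ between members of one home. For such factors, ignoring households can be neutral or conservative, as step 5 shows.
- **The planned precision is not wrong.** A reader might infer that the ±5-point target fails. It does not: at DE 1.5 with 585 evaluable per sex the half-width is ±4.96. Only an interval later computed without the household would be too narrow.
- **DE 1.5 within one sex is an upper scenario under the plan's own assumptions.** It needs all three infected members to share that sex. With mixed households the within-sex effect is smaller; 1.5 fits an estimate pooled over both sexes better.

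It is also true that the study is observational, that its sample size is called tentative and its subgroup analyses exploratory, and that point estimates of the proportion do not change. This lowers the urgency but leaves the primary interval unprotected.

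**Conclusion.** The point holds as a gap between the sample size and the analysis methods. Household clustering is assumed and quantified in the first and has no counterpart in the second.

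If the methods are run as written, the interval for the primary 12-month proportion is too narrow and tests of household-level or environmental factors are too liberal. The size rests on the plan's p = 0.50, ICC 0.25 and 10% loss, and on the cluster size that applies within one sex: about 89% coverage and 11% type I error with three, about 92% and 8% with two. The true ICC is unknown, so these are scenarios and not predictions.

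The documents do not support the broader readings that independence is the stated plan, that all p-values are too small, or that the planned precision is missed. The number of participants needs no change. The variance method should be settled before analysis, because it determines the reported precision of the primary outcome.

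**What to change.** State in the analysis methods that the household (index case plus enrolled contacts) is the independent cluster:

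- **Primary proportion and Kaplan-Meier estimates:** household-clustered or household-bootstrap 95% intervals.
- **Repeated binary outcomes:** GEE clustered on household, with visits nested within person.
- **Cox models:** robust variance aggregated by household, or a shared household frailty.
- **Clinic:** keep as a stratum or covariate, as already planned.

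Keep a household identifier in the de-identified analysis dataset. The article describes only a unique participant number and a code linked to a master key (Participant enrolment; Data management). It does not describe a variable that ties contacts to their index case, so this needs to be confirmed while the link can still be made.

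The cost is some wording, one coded variable and wider reported intervals: ±4.96 instead of ±4.05 points per sex under the plan's assumptions. The sample size already allows for that width.
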